## Abstract

**Background:**

Australian farming communities have up to twice the suicide rate of the general population. Men, particularly, demonstrate debilitating self- and perceived-stigma associated with an experience of suicide. The Ripple Effect is aimed to reduce suicide stigma within the social, cultural, geographical and psychological contexts in which it occurs.

**Methods:**

A mixed-method design with multi-level evaluation will be effected following the development and delivery of a personalised website experience (combining shared stories, education, personal goal setting and links to resources) to farming men, aged 30–64 years, with an experience of suicide. Pre- and post-surveys will be used to assess changes in self- and perceived-stigma and suicide literacy. Online feedback from participants and semi-structured interviews during follow-up will be thematically analysed.

**Discussion:**

This project will provide information about increasingly accessible, innovative approaches to reducing the debilitating health and wellbeing effects of suicide stigma on a population of Australia’s farmers.

**Trial registration:**

This research protocol was registered with the Australian New Zealand Clinical Trials Registry (ANZCTR) (ACTRN: ACTRN12616000289415) on 7^th^ March, 2016.

## Background

Suicide rates continue to be of concern in Australia, with recent figures of 12.2 per 100,000, of which approximately 75% of deaths were male [1]. Despite similar prevalence of diagnosed mental health conditions in metropolitan and rural areas [2], rural populations are at greater risk of suicide [3]. Within the rural population, farmers—defined by occupation—were identified as dying by suicide at up to twice the rate of the general employed population [4, 5]. The vast majority of farmer suicides were male and aged between 15 and 54 years [5]. These figures do not include individuals not defining themselves as farmers (for example, people with off-farm employment, retired farmers, self-identified ‘farmer’s wives’).

Australia’s male farmers have frequently been identified as conforming to normative behaviours encouraging self-reliance, risk-taking behaviour, a practical solution-focus to problems and an avoidance of emotional vulnerability. This combination leads to an increased risk of suicide, and an increased vulnerability to self-stigma and perceived-stigma when farmers are affected by suicide [6–8].

Suicide stigma is the single strongest correlate with grief difficulties and is associated with ongoing suicidal ideation [9]. Research has clearly identified self-stigma and perceived-stigma among those with a lived experience of suicide, including those bereaved by suicide [10, 11] and those who have attempted suicide [12, 13].

In order to attempt to reduce the stigma of suicide among male farming community members, it is first necessary to understand the socially constructed nature of stigma [14]. The social, cultural and contextual influences on self-stigma and perceived-stigma experienced and expressed by male farming community members must be recognised. As such, this community of interest requires a specifically adapted response [15].

### Impact of self-stigma and perceived-stigma

#### Suicide reporting

Where suicide stigma is prevalent, concealment of cause of death is not uncommon. Where concerns about stigma and confidentiality exist there may also be reduced reporting of suicide [16], particularly given the close social ties within farming communities, where anonymity is low and suicide stigma exists [6, 17].

#### Help seeking

Stigma is one of the most significant barriers to people talking about their suicide ideation and engaging with health services [12, 18]. Self-stigma and perceived-stigma reduces the opportunity to seek and engage professional assistance, particularly if prior contact has been unhelpful or negative [6, 12]. Internationally, men have been identified to experience higher levels of self-stigma and perceived-stigma around psychological problems, particularly those aged between 35–64 years and those who had never received help for psychological problems [19]. Kolves and colleagues [20] described the aversion to help-seeking relative to farming communities as including the stigma reinforced by the traditional masculinist paradigm of farming, the heavy and unrelenting work demands, the lack of access to physical and mental health services and a traditional focus on ‘practical’ problem solving as opposed to seeking help (see also [2, 21–25]). The public stigma associated with seeking psychological help may be internalised as self-stigma and perceived-stigma [26]. This is compounded by the tendency of rural farming community members to delay seeking help until symptoms are so severe as to prohibit one from fulfilling their farming role [27]. For male farming family members impacted by suicide, the need to avoid emotional vulnerability, maintain status and maintain self-reliant patterns of behaviour, reduces access to help even further [7, 28]. Asking for help, particularly for emotional problems, is simply not in the lexicon of many male farming community members and is not recognised within the farming family identity [7]. This is further exacerbated when associated with feelings of weakness, shame, guilt, selfishness and the sense of rejection often associated with the self-stigma and perceived-stigma accompanying a lived experience of suicide [29, 30]. Consequently, those experiencing suicide ideation and those who have attempted suicide are likely to obscure their behaviour [18] and avoid seeking assistance early in the suicidal process [30].

#### Social connection

Self-stigma and perceived-stigma in people with a lived experience of suicide leads to a perception of negative judgement, an avoidance of discussing the experience and their grief with other people [31] and further withdrawal from usual sources of social connection [11], particularly following suicide bereavement [11, 32]. This tendency for social withdrawal further restricts people’s access to the protection from vulnerability that effective social support can provide [18], increasing the potential risk for psychological distress and ultimately the ongoing cycle of suicide. This threat to social interaction and support is more challenging for suicide than other types of loss [33]. Social withdrawal is not only an entrenched passive process; those experiencing self-stigma and perceived-stigma may also actively stimulate avoidance and rejection by others [9]. In rural farming communities, where tightly integrated patterns of working and living are frequent, social disconnection may have a life-altering effect.

#### Ongoing cycle of suicide risk

A lived experience of suicide—whether through suicide ideation, attempted suicide, caring for someone who has attempted suicide, suicide bereavement or being touched by suicide in some other way—significantly increases both the ongoing risk of suicide and threats to mental health and wellbeing [12, 34–36]. Stigma increases the risk of suicide for those already suffering psychologically [19].

### Reducing self-stigma and perceived-stigma

Reducing self-stigma and perceived-stigma associated with a lived experience of suicide has numerous benefits. Firstly, de-stigmatisation improves communication between those with a lived experience of suicide and support networks, thus improving the opportunity for appropriate and acceptable intervention [37]. Secondly, while ingrained, socially constructed factors may restrict help-seeking, reducing self-stigma and perceived-stigma has been described as a way to reduce this barrier [28]. Thirdly, suicide stigma is one of the greatest barriers to generating good quality, accurate data about suicidal behaviour [18]. Reducing self-stigma and perceived-stigma may allow for greater openness from those with lived experience; increasing the knowledge base and enabling the development of appropriate support for those affected. Fourthly, disrupting the negative feedback of self-stigma and perceived-stigma will, over time, lead to a virtuous cycle [38] of reducing the personal and structural stigma of suicide in the broader farming community. Finally, the combination of knowledge, attitude and behaviour change has been suggested as the most effective way to reduce self-stigma and perceived-stigma, particularly through the facilitation of disclosure and the encouragement of positive social contact [38].

### Identifying gaps in stigma reduction research

The funding body for the Ripple Effect—*beyondblue*—identified a number of gaps in stigma research when developing a rationale for the study approach and target sample. These included:There was a dearth of evidence about digital interventions as a stigma reduction strategy, despite suggestions that the potential for widespread dissemination through digital communication is likely to play a role in stigma reduction [39].There was a lack of programs targeting the needs of people aged 30–64 years, when compared with those for people under the age of 30 years (*beyondblue*, unpublished data, 2013).Digital engagement was identified as dropping off after the age of 64 years (*beyondblue*, unpublished data, 2013).Perceived-stigma was identified as being higher in men aged 30–64 years (*beyondblue*, unpublished data, 2013).

The aim of this protocol is to describe the development, methodology (as outlined in the wireframe in Fig. 1) and proposed evaluation of the Ripple Effect—a digital intervention designed to reduce the self- and perceived-stigma associated with an experience of suicide for men from the Australian farming community aged between 30 and 64 years.

**Fig. 1 Fig1:**
[figure not shown]
Wireframe of the Ripple Effect intervention

## Methods/design

### Study design

The Ripple Effect encourages participation from a strengths-based perspective working with, rather than against the normative behaviours present in Australian male farmers (e.g. participation as a way of helping your farming community and presenting problems as solvable). Personalised progression through the Ripple Effect allows for targeted and relevant information to increase knowledge, influence attitudes and facilitate behaviour change. Access to additional appropriate support resources is built into the intervention.

The study is designed to include quantitative, qualitative and evaluation components.QuantitativeA non-randomised controlled trial will be used as the quantitative study design. The Ripple Effect website is the intervention and outcomes to be assessed are self-stigma and perceived-stigma about suicide and suicide literacy.QualitativeThe qualitative element of the study design will assess participants’ experience of suicide stigma—including how this influences patterns of help seeking—via short answer questions posed throughout the participation experience.EvaluationEvaluation of the Ripple Effect will occur:At the pilot stage via an online survey and verbal feedback.At the post-intervention stage using a 7-point Likert scale, with additional opportunity for including comments.At follow-up via semi-structured qualitative interviews.

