### Study population

The target population (stipulated by beyondblue, the funding body) are men from the Australian farming community aged 30–64 years who self-identify as having an experience of suicide—bereaved by suicide, attempted suicide, cared for someone who has attempted suicide, had thoughts of taking their own life, or been touched by suicide in some other way. The authors recognise that all members of the rural farming community are likely to be affected by suicide to some degree and believe the Ripple Effect will have benefit beyond the target population. Given this, the primary analysis will focus on men from the farming community with an experience of suicide aged 30–64 years. However, males outside of the target age and females will not be restricted from participating in the Ripple Effect website, and will be included in secondary data analysis. Membership to the farming community will be self-identified. Participants are required to be 18 years of age of over.

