### Data collection

Data collection will be via de-identified individualised digital interaction with participants, mapping their pattern of participation and change across time. Upon registration and prior to exposure to the intervention, participants will complete the Stigma of Suicide Scale - Short Form (SOSS) [42]—adapted to measure self-and perceived-stigma—and the Literacy of Suicide Scale (LOSS) [44].

The Ripple Effect intervention will be undertaken flexibly—participants can self-pace over a maximum 12-week period to complete the five core components. Participants are able to move in and out of the intervention as it suits them. The nature of the registration system allows for people to pick up where they left off. A personal profile page allows participants to identify their progress through the intervention. Participants will receive an email/SMS reminder if they have not logged in to the Ripple Effect after a certain period of time (determined by the participant).

On completion of all of the core content, participants will again complete the SOSS and LOSS tools (post-test). Participants who do not complete all core units will be sent an electronic reminder encouraging them to complete the post-test. Completing participants (all core content of the intervention) will be invited to participate in a semi-structured follow-up interview about their experience of participation in the Ripple Effect. A researcher with doctoral-level experience in interviewing farmers with an experience of suicide will conduct the interviews.

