### Data analysis

The SOSS short form (primary outcome measure) and LOSS (secondary outcome measure) will be administered at the beginning, and following completion of the Ripple Effect as an exit survey. The comparison of pre and post data will indicate changes of both stigma and literacy variables of participants in response to the intervention. Analyses will be performed in SPSS version 23 or later. The full analysis set (FAS) will be used adhering to the intention to treat principle (ITT). This will be complemented with analysis of a per protocol set (PPS) that only includes those who have completed the core components (defined as ‘completers’—participants who have worked their way through the core content and completed pre and post measurement of stigma and literacy). Comparing the ITT with the PPS will provide a sensitivity analysis for both the SOSS and LOSS. Paired t-tests will be used to assess the effect of the intervention over time (pre- and post-Ripple Effect). In the event some participants have missing data for the post intervention assessment of SOSS and LOSS, t-tests will be replaced by a mixed model analysis using the method of residual (or restricted) maximum likelihood (REML). Supplementary analyses will include measuring changes in the SOSS and LOSS in relation to the exposure to the intervention, with exposure defined as number of core units completed. Two-sided tests will be used with a level of *p* < 0.05 determining statistical significance.

Interview data will be thematically analysed based on indications of stigma reduction, and changes in help seeking behaviours and knowledge.

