### Outcomes

The Ripple Effect’s outcomes will include:Learning and reporting about what works to reduce self-stigma and perceived-stigma associated with an experience of suicide within the farming community (as measured by the SOSS [42]).Learning and reporting about what works to increase literacy of suicide within the community of farming (as measured by the LOSS [44]).Strengthening participants’ self-perception to enable them to assist others who are suffering, thereby reducing the self-perception of shame and isolation often associated with an experience of suicide.Increasing the knowledge base of suicide and its experience, and the experience of associated stigma, in rural farming communities.Increasing the knowledge of appropriate and acceptable ways to deliver social and emotional wellbeing messaging to members of the farming community.

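### The quantitative design is labelled a controlled trial, but it has no comparison group; it is a single-group, uncontrolled pre-post study, and its causal wording claims more than it can show

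*Protocol article*

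**What the plan says.** The protocol article, Study design (Quantitative), states that a "non-randomised controlled trial will be used as the quantitative study design". The next sentence names a single condition: "The Ripple Effect website is the intervention and outcomes to be assessed are self-stigma and perceived-stigma about suicide and suicide literacy".

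Data collection gives one path for everyone. "Upon registration and prior to exposure to the intervention, participants will complete the Stigma of Suicide Scale - Short Form (SOSS", and likewise the literacy scale. Afterwards, "On completion of all of the core content, participants will again complete the SOSS and LOSS tools (post-test". Table 2 has pre-, during- and post-intervention columns and no group column.

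The Sample size section bases the calculation on the pre/post difference in the stigma score and gives one recruitment total, 473.

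In Data analysis, "Paired t-tests will be used to assess the effect of the intervention over time". A REML mixed model replaces the t-tests if post-intervention data are missing. The same section says that the pre/post comparison will show "changes of both stigma and literacy variables of participants in response to the intervention". The section on limitations and strengths covers connectivity, access to technology and generalisability. It does not mention the absence of a control group.

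**The concern.** A reader who sees a non-randomised controlled trial expects a concurrent group that did not receive the intervention, and grades the evidence accordingly. Without such a group, the mean change among users combines any effect of the website with several other things:

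- answering the same scales a second time;
- regression to the mean;
- outside events during a self-paced period of up to 12 weeks;
- the selection of those who reach the post-test.

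A paired test asks only whether the mean change differs from zero. It does not say what caused the change. The Discussion intends the results to inform policy, service delivery and health promotion, so the label and the causal phrases affect how far the findings will be relied on.

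**Working it through.** **1. Is there a comparison group anywhere?**

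| Place in the protocol article | What it describes | Comparator? |
|---|---|---|
| Abstract, Methods | Pre- and post-surveys | No |
| Study design | One condition, the website | No |
| Study population | Women and men outside 30–64 may also use the website; secondary analysis | No, they are exposed too |
| Table 2 | One measurement schedule | No |
| Data collection | Everyone: test, website, test | No |
| Sample size | Pre/post difference, one total | No |
| Data analysis | Paired t-test or REML mixed model; no group term mentioned | No |

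The non-target users are not controls, since "males outside of the target age and females will not be restricted from participating in the Ripple Effect website". The supplementary analysis by number of core units completed compares self-selected levels of exposure within the one group. The intention-to-treat versus per-protocol comparison also stays within that group.

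**2. Does the sample size hold a control arm?**

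Inputs (Sample size; sidedness from Data analysis): d = 0.2, power 0.80, two-sided α = 0.05, attrition 20%.

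- Independent two-sample t-test: 393.4, rounded up to 394 per group. Power is 0.7996 at 393 and 0.8006 at 394.
- Attrition applied as n × (1 + 0.2): 394 × 1.2 = 472.8, rounded up to 473. This reproduces the stated target.
- Two groups on the same inputs would need 2 × 394 = 788 completers.

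The target is therefore one group's worth, which agrees with the text in showing no control arm.

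**3. How often would a non-specific shift be declared significant?**

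Assume no true intervention effect and a mean shift of δ, in units of the score SD, from other causes. The SD is taken as equal before and after. Pairs: 473 × 0.8 = 378.4, taken as 378. The pre-post correlation r is not given in the article, so a range is assumed.

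The standardised mean change is dz = δ / √(2(1 − r)). The paired t-test then has noncentrality dz × √378, with √378 = 19.44, and is compared with a two-sided 5% critical value of about 1.97.

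| Shift δ | r = 0.3 | r = 0.5 | r = 0.7 |
|---|---|---|---|
| 0.1 SD: dz | 0.085 | 0.100 | 0.129 |
| 0.1 SD: noncentrality | 1.64 | 1.94 | 2.51 |
| 0.1 SD: declared significant | 37% | 49% | 71% |
| 0.2 SD: dz | 0.169 | 0.200 | 0.258 |
| 0.2 SD: noncentrality | 3.29 | 3.89 | 5.02 |
| 0.2 SD: declared significant | 91% | 97% | >99% |

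**The case against.** The strongest reply is that the label appears once and the rest of the article is openly pre-post: the abstract, the sample size and the analysis all say so, and no between-group contrast is promised. That is true. It makes the label an error that other sections expose, but it does not make the label right, and the causal phrases in Data analysis remain. Saying that participants act as their own controls describes a pre-post study, not a controlled trial. Nor can this be left to a fuller document, because the article itself fixes the label, the sample size and the primary test, and they conflict.

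Some safeguards deserve credit. The full analysis set, the REML model for missing post-tests, the per-protocol comparison and the reminder to non-completers partly address selective completion. Anonymous participation may reduce socially desirable answering. None of these replaces a comparison group.

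Several stronger readings are not supported:

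- **That 473 is too few.** For the single-group contrast it is ample. If d = 0.2 is the standardised mean change, 199 pairs suffice for 80% power and 378 pairs give about 97%. The 788 completers matter only if a control arm was intended.
- **That the study can learn nothing about which elements help.** The Outcomes section lists "Learning and reporting about what works to reduce self-stigma and perceived-stigma associated with an experience of suicide". This is an aim of a mixed-method study with curated content, an analysis by units completed and interviews. These do not give controlled component effects, but the aim does not rest on the paired test alone.
- **That concurrent campaigns will bias the result, or that the registration is wrong.** The article documents no such campaign, and the registry record was not available for this review.

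**Conclusion.** The point holds. The article claims a design property, a control, that nothing else in it supports. What it describes is a single-group, uncontrolled pre-post study. The quantitative analysis can estimate change among users but cannot attribute that change to the website.

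The finding rests on the text and on the exact reproduction of 473 from one group's size. It needs no assumption. The percentages for a shift of 0.1 or 0.2 SD are illustrations. They depend on the assumed shift, the assumed correlations of 0.3 to 0.7 and the planned 20% attrition. The article gives no evidence that a shift of either size will occur. The 0.2 SD row at r = 0.5 is the study's own power at dz = 0.2, read for a shift from another cause. It shows that the test cannot tell the two apart.

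A reader might infer that the results will inevitably be presented as controlled evidence. The article does not show that. It shows a label and wording that would allow it. The correction is still needed, because it changes what the study may conclude.

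**What to change.** 1. **Study design:** replace the controlled-trial label with *single-group, uncontrolled pre-post study*.
2. **Data analysis:** replace the phrases about the effect of, and response to, the intervention with *change from pre- to post-test*. State that the primary quantitative conclusion is limited to change among users.
3. **Limitations and strengths:** add that there is no control group, so repeat testing, regression to the mean, outside events and selective completion cannot be separated from the intervention. Note that the mixed model and the per-protocol comparison only partly address the last of these.
4. **If a comparison group does exist:** describe it, make the between-group difference in change the primary contrast, and restate the sample size or power for that contrast.

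Items 1 to 3 change wording only; data collection, the planned tests and the recruitment target can stay as they are. The cost is a weaker but correct claim. Item 4 would need a new analysis and a new calculation.
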